## Abstract

**Background:**

Diabetes prevalence is increasing and current methods of management are unsustainable. Effective approaches to supporting self-management are required. The aim of this randomized controlled trial is to establish whether supported telemetric monitoring of glycemic control and blood pressure results in reductions in glycosylated hemoglobin (HbA1c; the primary outcome of a measure of long-term glycemic control) and secondary outcomes of blood pressure and weight among people with poorly controlled diabetes compared to a control group receiving usual care.

**Methods/Design:**

Design: multi-center, randomized controlled trial with embedded qualitative study.

Setting: primary care in Lothian, Kent, Glasgow and Borders regions in the UK.

Participants: people with type 2 diabetes and confirmed HbA1c >7.5% (58 mmol/mol).

Intervention/comparison: randomization to intervention or control groups will be performed by the Edinburgh Clinical Trials Unit. Participants in the intervention group will be shown how to use blood glucose and blood pressure monitors and weighing scales which use Bluetooth wireless technology to transmit readings via modem to a remote server. These participants will be asked to provide at least twice weekly measurements of morning and evening blood glucose and weekly measurements of weight and blood pressure. Measurements will be checked at least weekly by practice nurses who will contact the patients to adjust therapy according to guidelines and reinforce lifestyle advice. Participants in the control group will receive usual care. All participants will receive an individual education session.

Follow-up: measurements will be performed at practices 9 months after randomization by research nurses blinded to allocation. The primary outcome measure is HbA1c and secondary outcomes measure are daytime systolic and diastolic blood pressure, weight and cost per quality-adjusted life year.

Analysis: intention-to-treat analyses will be performed. The sample size of 320 participants allows for 20% drop-out and has 80% power at 5% significance to detect a 0.5% absolute (6 mmol/mol) fall in HbA1c in the intervention group. The qualitative study will explore the experiences of patients and professionals using the intervention.

**Trial registration:**

Trial registration number ISRCTN71674628

## Background

The prevalence of diagnosed diabetes is increasing across the world and, in Scotland, has increased from 3.9% to 4.7% in people of all ages between 2006 and 2011 according to the annual Diabetes Survey [1]. Estimates of total (both diagnosed and undiagnosed) diabetes from the Association of Public Health Observatories model for people over 15 years of age in Scotland suggest that the prevalence will increase from 6.7% in 2010 to 8.6% in 2030 [2]. Annual healthcare costs of a patient with type 2 diabetes are over six times higher than the costs of a person without, largely due to the development of diabetes-related complications. However, control of blood glucose and blood pressure (as well as management of dyslipidemia) among people with diabetes reduces complications and mortality [3-5].

The current medical model for managing diabetes does not necessarily engage individuals in a self-management approach, is expensive and often not very effective partly because therapeutic inertia may result in reluctance to change treatments. Effective chronic disease management should not only reduce costs but also improve quality of care. A study in the US has found that providing healthcare professionals with current patient information improved care and reduced costs [6]. Systematic reviews indicate that engaging patients in self-monitoring and management can improve clinical outcomes in asthma [7] but the evidence that self-monitoring alone is beneficial in people with type 2 diabetes [8] is less clear. This may be because adherence to both lifestyle advice and prescribed medication for these groups is poor generally [9] but also because feedback from clinicians is often infrequent, potentially adding to patient anxiety in the presence of abnormal self-monitored readings [10].

As described previously in the protocol for a trial of telehealthcare among people with chronic obstructive pulmonary disease from our group [11], several health service policies support the need to establish the cost-effectiveness of supported self-monitoring: shifting the balance of care for people with chronic conditions to primary care [12,13]; the drive for technological solutions to healthcare problems [14]; and the importance of expert patients and self-management of long-term conditions [15,16]. While some evidence can be gleaned from international research into telemetric solutions for chronic disease management and there are encouraging results from UK and international pilot studies [17-21], further research into the cost-effectiveness of these interventions is required, particularly within the National Health Services in the UK [22]. The Telescot research program was designed using frameworks for the development and evaluation of complex interventions [23,24]. Building on existing literature [17,25,26], and in an iterative process using insights from completed and on-going exploratory and pilot work [27], we have designed several complementary Phase III randomized controlled trials. These will evaluate how telemetry-aided, supervised self-monitoring affects the management of long-term conditions in four different contexts (largely asymptomatic conditions using the example of hypertension; symptomatic, potentially unstable and progressive conditions using the example of chronic obstructive pulmonary disease; an older, more disabled group with challenging management targets using the example of hypertension among stroke survivors; co-morbid conditions using the example of diabetes, hypertension and weight management). This paper describes the protocol for the latter trial in which the aim is to establish whether supported telemetric monitoring of glycemic control and blood pressure results in reductions in glycosylated hemoglobin (HbA1c; the primary outcome of a measure of long-term glycemic control), and secondary outcomes of blood pressure and weight among people with poorly controlled diabetes compared to a control group receiving a single education session in addition to usual care.

## Methods/Design

### Design/setting/participants/ethical approval

The Telescot diabetes trial is a randomized controlled trial of supported telemetric monitoring of glycemic control, blood pressure and weight of 9 months duration with a primary outcome of HbA1c, a measure of long-term glycemic control. Secondary outcomes include blood pressure and weight and will be measured by research nurses blinded to allocation group. The setting for the trial is primary care in Lothian, Kent and Borders in the UK. Participants will have poorly controlled type 2 diabetes (defined as HbA1c>7.5% (58 mmol/mol)), be over 17 years of age, have a mobile telephone signal available at their home and each participant will have given informed consent. People with very high blood pressure (>210/135 mmHg), who have hypertension or renal disease managed in secondary care, have had treatment for a cardiac event, or other life-threatening illness within the past 6 months or have had major surgery within the last 3 months, are unable to use self-monitoring equipment, have atrial fibrillation that has not been successfully treated or are pregnant will be excluded. Approval of the trial, which will be conducted to comply with the Declaration of Helsinki, has been obtained from the South East Scotland ethics committee 2 (reference number: 10/S1102160).

### Recruitment

We will recruit socially diverse practices to the trial using both the Scottish and English Primary Care and Diabetes Research Networks. We will make use of the network of practices in Lothian we have established during a previous blood pressure trial, who are familiar with the technology and have already expressed a willingness to take part. We will also use the networks and contacts provided by our grantholders to extend recruitment beyond Lothian to Kent and Borders. Training for the practices will be provided by the research team.

Diabetes registers in participating practices will be searched to identify potential participants with HbA1c>7.5% (58 mmol/mol). Potentially eligible patients will be sent the study materials by their general practice with a covering letter and asked to contact the researcher if they are interested in participating. Once a patient has indicated interest in participating they will be invited to a clinic in their general practitioner’s (GP’s) surgery run by a research nurse. At the initial appointment the nurse will go through the study information with the patient, take written informed consent (which will cover consent to have their eligibility checked as well as their consent to take part in the trial), check potential eligibility, ask the patient to complete a short questionnaire on their demographic characteristics, past and current self-monitoring of blood pressure and blood glucose, collect a blood sample for HbA1c and cholesterol measurement, a urine sample for sodium:creatinine ratio and initiate ambulatory blood pressure monitoring using the Spacelab Ambulatory Blood Pressure Monitor (ABPM) [28]. The nurse will also explain the process for recruitment and potential randomization if patients are eligible.

All patients will be loaned an ABPM with which they can monitor their blood pressure for 14 hours. However, if they wish they can delay collecting ABPM data until after the result of their HbA1C is available and their eligibility is confirmed. Once the HbA1c result is available, any ineligible patients will be telephoned to let them know that they do not need to return for a second appointment to gather baseline measurements. Patients’ ABPM results will be released to the practice.

### Baseline measurements

At their second appointment, prior to randomization, participants will have the following baseline measurements taken: smoking history, height and weight, and exhaled carbon monoxide. In addition they will be asked to complete a range of questionnaires to collect information on anxiety/depression [29], quality of life [30], self-efficacy [31], medication adherence [32], physical activity [33], exercise tolerance [34], knowledge of managing diabetes [35] and ethnic group, based on categories included in the 2011 Census [36].

Randomization will be carried out remotely at the Edinburgh Clinical Trials Unit to ensure adequate concealment. We will use minimization with a random element based on age (<70 or ≥70 years of age), sex, location (that is, Lothian, Kent, Glasgow or Borders) use of two or more diabetes drugs, use of three or more hypertension drugs and glucose self-monitoring history in order to make sure that these factors are distributed equally between intervention and usual care groups. The allocated treatment code will be generated by the Edinburgh Clinical Trials Unit over the internet (with a telephone back-up option if required). The participant will then be informed about the arm of the trial to which they have been assigned and given appropriate information and demonstration of equipment if allocated to the intervention group. All randomized participants will be included in the intention-to-treat analysis. All participants, regardless of allocation group, will be seen by a healthcare professional from the practice trained in the management of type 2 diabetes who will assess current control, optimize management in line with Scottish Intercollegiate Guidelines Network and National Institute of Health and Clinical Excellence (NICE) guidelines and deliver a one-to-one standardized education session.

It is not possible to blind clinicians or patients to the allocation group but baseline data collection will be undertaken by the research nurses before randomization takes place. Patients will be requested not to reveal their allocation to research nurses undertaking follow-up measurements, although we recognize that inadvertent references by the patients or in their primary care record may reveal their allocation. The use of objective outcomes (HbA1c, ambulatory blood pressure, weight, validated questionnaires) will also reduce the possibility of bias. Patients will be asked not to reveal which group they are in or to return their equipment until the final monitoring has been carried out. The research nurses will be asked to record unblinding prior to the final assessment.

### Intervention

Patients in the intervention group will be given blood pressure and blood glucose monitors and weighing scales which use Bluetooth to transmit readings via a (supplied) modem to a remote server. The user may securely access their record on the server at any time (either at home if they have internet access, or in a library or other public internet access point). Their GP and practice nurse will also be able to access this record via the Internet. Users will also receive regular (monthly) feedback based on their blood pressure and blood glucose over the past 10 readings which will be sent by post or email according to the patient’s wishes.

Participants will be trained in use of the equipment and the demonstration will be backed up by written information. The written information pack will also contain leaflets about initiating or maintaining lifestyle changes and how long it is likely to be before any lifestyle or medication change will have an impact on their rolling average blood pressure or blood glucose. The suggested lifestyle changes will include weight control, reducing salt in the diet and increasing physical activity.

The user will also be given contact details for the practice nurse and encouraged to make contact by email or by telephoning at specified times if their blood pressure or blood glucose remains high, to discuss their treatment. In the event of a very high blood pressure (>220 mmHg) or very high blood glucose levels (>15 mmol/l) patients will be asked to repeat the measurements and, if they remain high, to contact their practice urgently for advice. Patients recording very low blood glucose (<4 mmol/l) will be advised to eat or take a glucose drink and, if hypoglycemia persists, to contact the practice. Practice nurses will be encouraged to review the readings they are sent about patients whose blood pressure or blood glucose remains high or persistently low or who have not checked their blood pressure or blood glucose within the agreed timeframe on a weekly basis. Practice nurses may choose to contact the patient to offer further treatment or support and will be asked to record such contacts in the normal practice electronic record. The nurses will also be asked to transfer the current average blood pressure and blood glucose into the primary care record.

Patients will be encouraged to check their blood pressure 10 to 20 times over the first seven days to establish a reliable average and then about 4 times a month if their average blood pressure is at or below the target of 130 mmHg. If blood pressure is above the target and any changes to lifestyle or medication are made, the users will be asked to undertake another more intensive period of monitoring (10 to 20 readings over seven days) after an appropriate time (usually 3 to 4 weeks depending on medication change) in order to establish the impact on the rolling average blood pressure. The guidance will not be restrictive as this tool is being provided for patients to use in order to understand their blood pressure better and to better manage their own health.

Patients in the intervention group will be asked to provide at least twice weekly measurements of morning and evening blood glucose and weekly measurements of morning weight. These measurements will be automatically forwarded to the study website and checked at least weekly by the practice nurse. Patients with high readings will be highlighted by the software for easy identification. The nurses will contact the patients by telephone, text or email to adjust therapy and reinforce lifestyle advice on the need for more or less intensive monitoring. Antihypertensive drug treatment may be altered every 4 to 6 weeks until mean blood pressure based on the last 10 readings is at or below the target of 130 mmHg. Treatment for diabetes will be altered according to the protocol based on guidelines every 4 weeks with the aim of maintaining consecutive fasting blood levels between 4 and 6 mmol/l. Patients who require the addition of insulin to their treatment during the course of the trial will be jointly managed by the practice nurse and GP along with specialist diabetes nurses at the local hospital (if appropriate) according to local practice, all of whom will have access to the telemetric data for patients in the intervention group. Algorithms for glucose and blood pressure management are given in the appendices.

### Control group

Patients in the control group will receive leaflets with lifestyle advice and usual care, that is attending the practice nurse or GP for appointments as normal. They will be asked about their use of self-monitoring of blood pressure and blood glucose at baseline and follow-up. Patients with uncontrolled blood pressure in our recent audit saw the nurse or doctor three or four times on average in 6 months and we would anticipate a similar number of attendances for patients with both uncontrolled glycemia and blood pressure. Patients requiring insulin during the course of the trial will be managed jointly as above with specialist diabetes nurse support. Throughout the trial, patients will be reviewed according to clinical need by their normal clinical advisors. Clinical care in both groups for patients in Lothian will be in accordance with NHS Lothian protocols which are based on the recommendations of national and international guidelines, and in other areas according to NICE guidance. Therapeutic algorithms for both controls and intervention will follow guidelines, based upon the NICE guidelines [37] using a standard stepped treatment program for blood glucose.

### Follow-up measurements

Participants will be seen by a researcher/research nurse blinded to their allocation at their GP practice 9 months after randomization. The follow-up appointment will include completion of questionnaires to collect information as at baseline, other than ethnicity, blood sample collection for HbA1c and cholesterol and fitting of the ABPM. Participants will be asked to return the ABPM the following day. Use of healthcare resources (number and duration of hospital admissions, including whether primary diagnosis was diabetes-related, practice and out-of-hours consultations, routine reviews for blood pressure or diabetes, prescriptions for antihypertensive and diabetes drugs and test-strips) and adverse events will be extracted from the participant’s electronic record by the researcher or research nurse at the follow-up appointment. Electronic records will be retrieved and analyzed for compliance with monitoring. The baseline measures (excluding height) will be repeated at the end of the 9 month follow-up period.

### Data collection and statistical analysis

Records will be kept of the numbers of practices and patients that were approached to participate in the study and the numbers and proportions of practices and patients that consented or declined to take part. Data from participating individuals will be entered from questionnaires and paper records by the researcher to a database. A random 10% sample will be checked for accuracy by independent trial staff. If we detect systematic errors we will re-enter all the data. Every attempt will be made to collect complete data on all of the participants.

Data analysis will be carried out by the Edinburgh Clinical Trials Unit. Data will be analyzed on an intention-to-treat basis, that is by allocation group regardless of compliance with the intervention. In the primary analysis we will remove patients with missing outcome data, but will perform sensitivity analyses to investigate the effect of this. Binary outcomes will be presented both as relative and absolute risk reductions. For HbA1c and blood pressure, and other normally distributed measurements that are taken at baseline and follow-up, adjustment for baseline measures will be performed using analysis of covariance. For the primary outcome, subgroup analyses will be performed based on sex, tertiles of age and socio-economic status (based on the Scottish Index of Multiple Deprivation derived from postcode) and tertiles of baseline HbA1c, home self-monitored systolic blood pressure and body mass index. These factors may all reasonably be hypothesized to influence the effect of the intervention. Subgroup analyses will be performed by adding any interaction between these factors and treatment into the analysis of covariance model and observing whether the fit of the model is statistically significantly improved. No interim analysis is planned.

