### Sample size calculation

There were 4440 people with type 2 diabetes, an HbA1c of >7.5% and systolic blood pressure of ≥135 mmHg on the Lothian diabetes register in 2008. This group reflects approximately 16% of people on the register with type 2 diabetes. Their mean (standard deviation) HbA1c was 8.8% (1.4%) and their mean (standard deviation) systolic blood pressure was 149 mmHg (13 mmHg).

Using these values, we calculate that a randomized controlled trial with 125 people completing each arm with no change in values in the control group at the end of the trial would have 80% power at 5% significance to detect a 0.5% absolute fall in HbA1c and a 5 mmHg fall in systolic blood pressure in the intervention group. In an earlier trial of telemetric monitoring of blood pressure, 60% of patients on a practice hypertension register agreed to take part and 82% were retained within the trial [38]; we anticipate similar recruitment and retention rates in this study. We therefore plan to recruit a total of approximately 320 patients to ensure two final group sizes of 125 people which will provide sufficient power (assuming that up to 20% of people may drop out of the trial). We anticipate that this will involve recruiting 25 to 30 large general practices to participate in the study.

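### The stated ANCOVA names only baseline adjustment and none of the six minimization factors; adding them would be a nearly free gain in precision if they are prognostic

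*Protocol article*

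**What the plan says.** **Allocation.** The Baseline measurements section of the protocol article states: "We will use minimization with a random element based on age (<70 or ≥70 years of age), sex, location". The list continues with four named regions and then "use of two or more diabetes drugs, use of three or more hypertension drugs and glucose self-monitoring history". The stated aim is an equal distribution of these factors between the arms.

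**Analysis.** The Data collection and statistical analysis section covers HbA1c, blood pressure and other normally distributed measures recorded at both visits. For these, "adjustment for baseline measures will be performed using analysis of covariance". The natural reading is the baseline value of the outcome being analyzed. Sex and age (as tertiles) reappear only in the subgroup analyses, as interactions added to this model. Location, the two drug counts and self-monitoring history do not reappear in that section.

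**Power.** The Sample size calculation section works from the raw register SD of 1.4% for HbA1c and takes no credit for any covariate.

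**The concern.** Minimization makes the arms more alike on the chosen factors than simple randomization would. If those factors also predict the outcome, the treatment estimate varies less from trial to trial than a model without them assumes. That model counts the balanced variation as random error. Its standard error is then too large, its confidence interval too wide, and its test rejects a true null hypothesis less often than 5%.

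What is at stake is precision from variables already recorded for every randomized participant. The error is on the safe side: it neither inflates false positives nor biases the estimated effect.

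**Working it through.** **Inputs from the Sample size calculation section**
- Effect, significance level and power: "80% power at 5% significance to detect a 0.5% absolute fall in HbA1c".
- SD of HbA1c: 1.4%.
- Completers: "a randomized controlled trial with 125 people completing each arm".
- Loss and total: "assuming that up to 20% of people may drop out of the trial"; "We therefore plan to recruit a total of approximately 320 patients".

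**Assumptions, because the document gives no figure**
- ρ: correlation of baseline with 9-month HbA1c.
- R²: share of the variance left after baseline HbA1c that the six factors explain.

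**Step 1: reproduce the plan's figure.** Two-sided 5%, 80% power:

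n per arm = 2 × (1.960 + 0.842)² × 1.4² / 0.5² = 123.1, so 124, against the stated 125.

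At 125 per arm, SE = 1.4 × √(2/125) = 0.177 and power = Φ(0.5/0.177 − 1.96) = 80.6% (80.3% by noncentral t). For dropout, 250/0.8 = 313, against about 320. The plan's arithmetic holds.

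**Step 2: degrees of freedom.** Age 1, sex 1, location 3 (the four regions in the minimization list), diabetes drugs 1, hypertension drugs 1, self-monitoring history 1 (taken as yes/no): 8 in all. With 250 completers, 250 − 3 − 8 = 239 remain.

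**Step 3: standard error and power.** Residual SD after baseline is 1.4 × √(1 − ρ²). With the factors added it is multiplied by √(1 − R²). Under perfect balance:
- SE ratio (baseline-only to adjusted) = 1/√(1 − R²).
- Baseline-only power = Φ((0.5 − 1.96 × SE_model)/SE_true), where SE_true = SE_model × √(1 − R²).
- Adjusted power from the noncentral t with 239 degrees of freedom.

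Example with ρ = 0, R² = 10%: SE_model = 0.177 and SE_true = 0.168. Baseline-only power = Φ((0.5 − 0.347)/0.168) = 81.9%; adjusted power = 84.2%.

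| R² | SE ratio | ρ = 0: baseline-only → adjusted | ρ = 0.5: baseline-only → adjusted |
|---|---|---|---|
| 0 | 1.00 | 80.6 → 80.3% | 90.3 → 90.1% |
| 2% | 1.01 | 80.8 → 81.1% | 90.5 → 90.7% |
| 5% | 1.03 | 81.2 → 82.3% | 90.9 → 91.5% |
| 10% | 1.05 | 81.9 → 84.2% | 91.5 → 92.8% |
| 15% | 1.08 | 82.6 → 86.2% | 92.1 → 94.1% |

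The change in power runs from −0.3 to +3.6 points at ρ = 0 and from −0.2 to +2.0 at ρ = 0.5. At ρ = 0.7 and R² = 15% the gain is 0.5 points (98.5 → 99.0%).

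**Step 4: simulate the allocation.** Perfect balance is an idealization, since the minimization has a random element and some participants are lost. The simulation used 320 randomized, an assumed biased coin of 0.8, 20% lost at random, ρ = 0.5, assumed factor frequencies and 3,000 runs per scenario.

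| R² | Baseline-only model SE vs empirical SE (no effect) | Type I error, baseline-only | Power, baseline-only → adjusted |
|---|---|---|---|
| 0 | 0.152 vs 0.155 | 5.2% | 91.0 → 91.0% |
| 5% | 0.152 vs 0.150 | 4.8% | 91.2 → 91.9% |
| 10% | 0.152 vs 0.147 | 4.4% | 91.5 → 93.4% |

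The adjusted model kept type I error at 4.8 to 5.1%. Simulation error on a type I rate is about 0.4 points. The perfect-balance formula 2Φ(−1.96/√(1 − R²)) gives 3.9% at R² = 10%, so it marks the extreme of the conservatism.

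**The case against.** The strongest reply is that this is silence in a condensed article. The text neither says that baseline is the sole covariate nor excludes the minimization factors, and a covariate list is a common item for an analysis plan that is not shown here. That stands as a caution: a reader might infer that the plan rules the factors out, and the document does not support that. It does not remove the point. The section describes a covariate adjustment and then adds interactions to it as a defined model, and sex, location or a drug count do not fit naturally under baseline measures of an outcome taken at both visits. Followed as written, the model leaves the factors out.

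Second, the loss is conditional. If the factors add nothing beyond baseline HbA1c, the baseline-only standard error is correct and adding them costs about 0.3 points of power or less. The document gives no R², so no firm figure is available. This stands in full.

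Third, a reader might infer that the trial is underpowered or its test invalid. Neither follows. The 80% was computed from the unadjusted SD, and baseline-only power is at least 80.6% in every scenario above. The departure in type I error is downward. Nor should one apply an R² defined after baseline adjustment to the raw-SD calculation and treat the result as typical: that amounts to setting ρ to zero and gives the largest gain, not the expected one.

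**Conclusion.** The point holds as a modest matter of efficiency. Allocation is balanced on six factors and the stated ANCOVA names none of them. Over an assumed R² of 0 to 15%, standard errors are 0 to about 8% wider than they need be. Adjustment changes power by −0.3 to +3.6 points, less at the top of the range once baseline HbA1c correlates with follow-up. Simulated type I error is about 4.4% at R² = 10%.

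Confidence is high in the direction and low in the size, which rests on ρ and R², neither of which the document gives. The document does not support a claim of invalid inference, lost planned power or deliberate exclusion of the factors. This is a free improvement, not a defect that must be repaired for the trial to be sound.

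**What to change.** In Data collection and statistical analysis, state the primary model as 9-month HbA1c on treatment, baseline HbA1c and the six minimization factors: age, sex, location, two or more diabetes drugs, three or more hypertension drugs, and glucose self-monitoring history. Add the same factors to the baseline-adjusted models for blood pressure and weight. Age may enter as continuous or as the band split at 70 years; choose one form in advance. Settle the list before outcomes are compared by arm, which also removes any later choice between adjusted and unadjusted results.

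Cost: one sentence and about 8 of roughly 250 degrees of freedom. The data are already collected for allocation, and the sample size needs no change.

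### The socio-economic subgroup analysis names only a Scottish deprivation index, so participants from Kent, a planned recruiting region, have no socio-economic tertile under the rule as written

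*Protocol article*

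**What the plan says.** The section on data collection and statistical analysis states: "For the primary outcome, subgroup analyses will be performed based on sex, tertiles of age and socio-economic status". Socio-economic status is defined there in one way only: "socio-economic status (based on the Scottish Index of Multiple Deprivation derived from postcode"). The test consists of "adding any interaction between these factors and treatment into the analysis of covariance model" and judging whether the model then fits significantly better.

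The regions are given in four places:
- Abstract, Methods/Design: "primary care in Lothian, Kent, Glasgow and Borders regions in the UK".
- Design/setting/participants/ethical approval: "The setting for the trial is primary care in Lothian, Kent and Borders in the UK".
- Recruitment: practices are sought "using both the Scottish and English Primary Care and Diabetes Research Networks", with a plan to "extend recruitment beyond Lothian to Kent and Borders".
- Baseline measurements: minimization uses "location (that is, Lothian, Kent, Glasgow or Borders").

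The lists differ on Glasgow, but all four include Kent. The article names no English deprivation index, no way of combining national indices, and no rule for a participant without a Scottish value.

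**The concern.** A Scottish index ranks Scottish areas, so a lookup by postcode returns nothing for Kent. A participant without a value has no tertile and cannot enter a model that contains the tertile-by-treatment term. The missing values would fall wholly on one region rather than at random.

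Three things are at stake:
- **Population.** The test would describe Scottish participants, although the article presents the subgroup analyses as analyses of the trial.
- **Model comparison.** A comparison of fit is valid only if both models use the same participants. If the model without the interaction keeps Kent and the model with it loses Kent, the two are not comparable.
- **Pre-specification.** If the gap is noticed only at analysis, someone must then choose a second index and a way to combine the two, possibly with outcome data in view.

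**Working it through.** **Step 1. Does the rule cover the trial's regions?**

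| Region | Where listed | Value on a Scottish index? |
|---|---|---|
| Lothian | all four places | yes |
| Borders | all four places | yes |
| Glasgow | Abstract; Baseline measurements | yes |
| Kent | all four places | no |

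The inconsistency about Glasgow has no bearing here, because Glasgow is in Scotland.

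**Step 2. Reproduce the plan's own figures.** Inputs from the sample size section: difference 0.5%, SD 1.4%, 80% power, 5% significance (taken as two-sided; the article does not say), 125 completers per arm, up to 20% drop-out.

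- n per arm = 2 × 1.4² × (1.960 + 0.842)² / 0.5² = 123.1, rounded up to 124. The plan has 125.
- Power with 125 per arm: SE = 1.4 × √(2/125) = 0.177; 0.5/0.177 − 1.960 = 0.86; power 80.6%.
- Recruitment: 250 / 0.80 = 312.5, so 313. The plan has approximately 320.

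The figures reproduce, and none of them depends on the deprivation index.

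**Step 3. How many participants are unclassified?** The statistical analysis section removes participants with missing outcomes from the primary analysis, so the base is the 250 planned completers. The Kent share is not given; 10% to 30% is assumed, with retention the same in every region.

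- 0.10 × 250 = 25
- 0.30 × 250 = 75

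The same shares of the 320 recruited would be 32 to 96, but that counts people who are not expected to be in the analysis.

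**Step 4. What does this do to the subgroup test?** As an illustration, take equal tertiles, 1:1 allocation, SD 1.4 and no gain from baseline adjustment. With m participants per tertile per arm:

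- SE of the difference in treatment effect between two tertiles = 1.4 × √(4/m)
- Power for a 0.5% difference between two tertiles = Φ(0.5/SE − 1.960)

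| Assumed Kent share | Completers left | m | SE | Power |
|---|---|---|---|---|
| 0% (all classified) | 250 | 41.7 | 0.43 | 21% |
| 10% | 225 | 37.5 | 0.46 | 19% |
| 30% | 175 | 29.2 | 0.52 | 16% |
| 50% (extreme) | 125 | 20.8 | 0.61 | 13% |

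For the 30% row: 175/6 = 29.2; 1.4 × √(4/29.2) = 0.52; 0.5/0.518 − 1.960 = −1.00; Φ(−1.00) = 0.16.

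Precision falls, but from a low starting point. The main effect of the gap is on which population the test describes.

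**The case against.** The strongest reply is that this is a condensed article. A parenthesis naming an index may be shorthand, and the lookup for English postcodes is a detail that an analysis plan could settle. That lowers the certainty that anyone would actually be lost. It does not remove the point, because the article names one specific index without qualification, and that index cannot be applied to one of the trial's own regions.

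A second reply is that little depends on this. It concerns one factor in a set of subgroup analyses, with about 21% power for a 0.5% between-tertile difference even when everyone is classified. The Discussion already lists the inability to identify patient subgroups that benefit more as a limitation. This stands, and it limits the severity.

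Stronger readings are tempting, but the documents do not support them:
- *Kent participants are excluded.* The article never says so. It is what follows if the stated rule is applied literally.
- *A Scotland-only result would be reported as trial-wide.* The article does not say how this subgroup result would be labelled.
- *Raw English and Scottish scores would be mixed in one set of tertiles.* Nothing in the article proposes this.
- *The treatment comparison would be biased.* Location is a minimization factor, so leaving out Kent should remove similar numbers from each arm, and the comparison among Scottish participants remains randomized. The cost is precision and a narrower population.

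**Conclusion.** The point holds as a minor-to-moderate issue. The stated definition gives Kent participants no socio-economic tertile, and the interaction test would in effect be confined to Scottish participants. About 25 to 75 of the 250 planned completers would be unclassified. That range rests on an assumed Kent share of 10% to 30% and equal retention across regions; the article anchors neither.

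A reader might infer that the trial's main conclusion is at risk. It is not: the primary analysis of covariance, the secondary outcomes, the randomization and the sample size do not use the index.

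**What to change.** Before outcome data are seen, amend the definition in the statistical analysis section:

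1. Classify each participant by the deprivation index of their own country: the Scottish index for Scottish postcodes and the English equivalent for Kent.
2. Form tertiles from each participant's national rank within their own country. Do not pool raw scores from the two indices.
3. Fit the models with and without the interaction on the same participants.

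If a second index is not wanted, state explicitly that this subgroup analysis is restricted to Scottish participants, and report it as such. A term for region could be added, but it is not needed to close the gap.

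The cost is a few lines of text and one more postcode lookup. The small downside is that national ranks are only approximately comparable between countries, which should be acknowledged when the result is reported.
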